### Intervention

The intervention consists of weekly befriending sessions from a trained volunteer for a four-month period, and is provided in addition to usual care. Befriending is defined as “acting or becoming a friend to (someone), especially when they are in need of help or support” [31]. Befriending conversations consist of neutral topics of interest to both parties, including discussions around hobbies, family, neutral news topics, and other topics to be negotiated between the two parties and tailored to individual interests. Volunteers undergo standardised training on how to conduct the intervention. A manual is provided for volunteers to refer to throughout their befriending experience (available on request). The training is delivered either face-to-face in small interactive groups or via online modules and video conference. Topics covered in the training session include: what to expect when visiting a RACF; characteristics of residents in RACFs; how to conduct befriending conversations; topics to avoid; what to do if a resident becomes upset; how to manage indications of elder abuse; key symptoms of depression and anxiety; how to communicate with someone with mild cognitive impairment; how much personal information to disclose; and how to say goodbye at the end of the intervention. The training includes reflective questions on the content and allows for individual variation in experience of RACF settings. Responses to the training are evaluated using pre and post questionnaires and ongoing refresher tests. Volunteers participate in focus groups to discuss their response to their befriending experiences.

At each RACF, befriending sessions are held face-to-face in a mutually agreed private setting or remotely via phone or video call depending on local biosecurity guidelines during the COVID-19 pandemic. Sessions may switch from one format to another depending on local circumstances. There is no required minimum length of time for each befriending session, however it is anticipated that each session will last for approximately 30–60 min and not more than 2 hours. The control group receives usual care during the assessment period, and participants are offered a volunteer befriender at the completion of their four-month assessment period, but the impact of these sessions will not be evaluated as part of the study.

### Outcome measurements

#### Primary outcome measure

The primary outcome in the study is depression, as measured by the GDS 15 [29], a reliable and valid screening tool for depression in older people. It comprises “Yes/No” questions about how the participant has felt over the past week. Of the 15 items, 10 indicate the presence of depression when answered positively and five indicate depression when answered negatively. Higher absolute total scores indicate increased depressive symptoms are present.

#### Secondary outcome measures

Secondary outcomes are anxiety, loneliness, social isolation and quality of life. These outcome measures will capture negative as well as positive effects. Anxiety is measured by the Geriatric Anxiety Inventory (GAI 20-item) [32], consisting of 20 “Agree/Disagree” items designed to assess typical common anxiety symptoms in older adults. Loneliness is measured by the UCLA Loneliness Scale [33], a 20-item scale designed to measure a participant’s subjective feelings of loneliness as well as feelings of social isolation. Participants rate each item as either Always (“I always feel this way”), Sometimes (“I sometimes feel this way”), Rarely (“I rarely feel this way”) or Never (“I never feel this way”). Social isolation is measured by The Lubben Social Network Scale-6 [34]. This scale is designed to gauge social isolation in older adults by measuring the number and frequency of social contacts with friends and family members. Health related quality of life is measured by the EQ-5D-5L [35] which comprises five dimensions: mobility, self-care, usual activities, pain/discomfort and anxiety/depression. Each dimension has five levels: no problems, slight problems, moderate problems, severe problems and extreme problems. The patient’s self-rated health is recorded on a vertical visual scale, where the endpoints are labelled ‘The best health you can imagine’ and ‘The worst health you can imagine’.

#### Descriptive measures

Demographic information about the participants is collected, including gender, date of birth, county of birth, date of admission to the residence, medical conditions and comorbidities as measured by the Charlson Comorbidity Index [36], activities of daily living capabilities as measured by the Aged Care Funding Instrument (ACFI) Activities of Daily Living domain which consists of questions about nutrition, mobility, personal hygiene, toileting and continence [37], marital/relationship status, highest education level and ethnic and gender diversity details.

#### Economic evaluation

An economic evaluation will be conducted to assess the cost effectiveness of the befriending intervention. The economic evaluation will take the form of a cost-utility analysis based on the outcome of quality of life as measured by the EQ-5D-5L. Health service utilisation data on the frequency and duration of access to primary care, emergency department visits, overnight hospital stays, psychiatrists, psychologists and other mental health practitioners are obtained from RACF records. Medications are obtained from the RACF records.

#### Qualitative measures

Qualitative methods are being used to increase our depth of understanding about befriending. Participants in the intervention arm are invited to participate in a short semi-structured interview at the end of the intervention. Participants are asked questions about their initial reactions to befriending, change in perception over time, benefits and disadvantages of befriending, matching of personalities, logistical issues such as frequency and intensity of visits and the format of the befriending. All volunteers are invited to participate in focus groups or individual interviews to gauge their perception of the befriending experience.

### Data collection and management

Data collection is performed by blinded research assistants trained to administer the outcome measures in a structured interview, with the exception of some data available from the resident’s RACF records, which is provided by the RACF staff. Inter-rater reliability between research assistants is tested regularly for the GDS 15, GAI 20-item and UCLA Loneliness Scale using the Kappa statistic to monitor consistency. Discrepancy in assessments (kappa less than 0.4) is discussed and consistent probing statements are used for each outcome measure to maximise consistency across time and between research assistants.

The qualitative interviews are digitally recorded and transcribed verbatim by a professional transcription service. A data monitoring committee is not needed because the trial is not testing a drug or device and any safety concerns associated with the trial have been reviewed by the ethics committee. Participants are informed that they can withdraw from the study at any time and any incomplete data is retained by the project team.

#### Assessment timepoints

Table 1 shows the timepoints when each outcome measure is conducted: at baseline assessment (T1), 2 months post commencement of intervention (T2) and follow-up assessment 4 months post commencement (T3).

**Table 1 Tab1:** Measures and assessment timepoints

Measure/Timepoint	Screen	T1 Baseline	T2 2 months post baseline	T3 4 months post baseline
GDS 15	✓		✓	✓
CSDD (from ACFI)^a^	✓			
PAS-CIS (from ACFI)^a^	✓			
GPCOG	✓			
Demographic data		✓		
GAI 20 item		✓	✓	✓
EQ-5D-5L		✓	✓	✓
UCLA Loneliness Scale		✓	✓	✓
Lubben Social Network Scale-6		✓		✓
Health service usage		✓		✓
Charlson comorbidity index		✓		✓
Medications		✓		✓
Satisfaction with befriending (qualitative data)				✓
Perceptions of befriending (qualitative data)				✓

^a^Provided to research team after resident provides consent to be involved in the study

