### Study design

The BEFRIENDAS study is an ongoing single blind pragmatic RCT comparing two groups of older people living in RACFs, one receiving weekly befriending for 4 months from a trained volunteer and the other receiving treatment as usual (TAU). As few previous RCTs of befriending have been conducted, TAU is an appropriate comparator. A clustered design is not necessary because the intervention is to be delivered at the individual level and not the RACF level. Furthermore, there is no evidence that RACFs have different policies on treatment of depression. Group allocation is blinded to the assessors but necessarily un-blinded to the participant. Participants undergo eligibility screening and assessments at three measurement time points: baseline prior to randomisation (T1), 2 months after the intervention starts (T2) and at the conclusion of the intervention 4 months post-baseline (T3). Figure 2 presents the flow of the participants through the study.

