#### Further eligibility screen conducted by research assistants to confirm eligibility

Geriatric Depression Scale 15-item (GDS 15) [29] score of 4 or greater as assessed by the research assistant.General Practitioner Assessment of Cognition (GPCOG) [30] score of 4 or greater as assessed by the research assistant.

Residents who are unable to give informed consent, have progressive, unstable medical or neurological illness, a diagnosis of dementia or who are under the age of 65 years are excluded from the project.

Volunteers administer the befriending intervention and participate in qualitative evaluation of the experience. Volunteers are a convenience sample recruited via volunteer recruitment websites, social media advertisement, word of mouth and through advertisements in industry newsletters. Volunteers are eligible to participate if:
over 18 years and have a valid police checkhave an up to date influenza immunisationassessed as suitable (according to availability, conversation skills and attitudes) in an interview with the volunteer coordinatoravailable for at least 6 months of volunteeringable to travel to the RACF where appropriatewilling to participate in training and ongoing supervision.

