### Sample size

We are aiming for a clinically significant change of greater than two points in the GDS. Based on the average effect size of 0.27 for short term befriending outcome studies of mostly older adults with depression in primary care settings, it is estimated that with data collection spread over a three-year period, and allowing for a higher than usual dropout rate of 20% given low life expectancy among RACF residents, recruiting 172 participants per study arm (total of 344 participants) would achieve 80% power, with a statistical significance of 0.05. It is anticipated that each volunteer recruited may only befriend one participant, so a total of over 500 volunteers will be recruited throughout the study. Recruitment strategies to achieve the sample include wide ongoing advertisement and presentations in industry meetings and publications, monitoring quotas and widening locations where needed.

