### Randomisation

Following the baseline assessment, participants are randomly allocated to the befriending intervention group or the TAU control group. Relevant concomitant care and interventions such as psychological interventions or anti-depressants are noted and considered treatment as usual. Randomisation is managed by a trial statistician who is not directly involved in the study. A computer-generated random sequence available to the trial statistician, but no other research staff, is used to produce random allocation using a randomised permuted block design with block size of two in order to maintain approximately balanced randomisation throughout the trial. Randomisation is provided to an un-blinded researcher via email to verify that the correct allocation has taken place. The un-blinded researcher notifies the participants about their allocation and arranges for the intervention to begin. Research assistants conducting the assessments are blinded to group allocation.

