### Data analysis

No interim analyses to inform stopping guidelines will be required. The balanced characteristics between the intervention and control arms will be assessed by comparison of all baseline characteristics between the two study groups using χ^2^ test for dichotomous variables and either ANOVA or Kruskal-Wallis test for continuous data. Comparison of descriptive data will be made between participants who completed the study and those who dropped out to assess differential attrition. The primary and secondary outcomes (change over time in depression, anxiety, loneliness and social isolation) will be analysed using negative binomial and logistic regressions utilizing the Generalised Estimating Equations (GEE) approach, a marginal model in which the effect of covariates on the outcome is averaged over individuals at each point in time and is compared over time [38]. An exchangeable working matrix will be used to account for correlation and dependence between repeated measurements on the same individual over time while adjusting for study covariates.

Data analysis will investigate possible mediating variables explaining any relationship found between befriending and depression symptoms. Possible intervening variables of interest will include baseline depression/anxiety (higher is worse); baseline cognition (higher is better); and intensity of befriending (more befriending sessions are better). For the economic analysis, utility based outcomes, generated from application of the EQ-5D-5L, will be used to calculate the cost per quality-adjusted life-year (QALY) gained. Costs will include staff time spent preparing and producing training materials in addition to staff time spent administering/managing the befriending intervention. Unit costs for the mental health service utilization data will be derived from published fee schedules. Incremental cost effectiveness ratios and their associated confidence intervals will be estimated and cost effectiveness acceptability curves for varying threshold values of cost effectiveness will also be presented. An assessment of the sensitivity of the results obtained to variation in measured resource use, effectiveness and/or unit costs will be undertaken using appropriate one-way and multi-way sensitivity analysis.

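### Table 1 gives the GDS-15 no T1 assessment, so its only scheduled pre-randomisation value is the entry score, and the article never says that the primary model adjusts for it.

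*Protocol article*

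**What the plan says.** Four parts of the protocol article bear on this.

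- **Study design:** "Participants undergo eligibility screening and assessments at three measurement time points: baseline prior to randomisation (T1", followed by T2 and T3. T1 is thus an assessment before randomisation.
- **Further eligibility screen:** entry requires a "Geriatric Depression Scale 15-item (GDS 15) [29] score of 4 or greater as assessed by the research assistant".
- **Assessment timepoints:** the text reads "Table 1 shows the timepoints when each outcome measure is conducted: at baseline assessment (T1" and goes on to T2 and T3. In Table 1 the GDS-15 row is ticked at Screen, T2 and T3 only. The GAI, EQ-5D-5L, UCLA and Lubben rows are all ticked at T1.
- **Data analysis:** "The primary and secondary outcomes (change over time in depression, anxiety, loneliness and social isolation) will be analysed" by negative binomial and logistic GEE with an exchangeable working matrix. The section says that study covariates are adjusted for but does not list them. Baseline depression appears once, among possible intervening variables in the search for mediators.

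No section says that the screening GDS-15 serves as the baseline, or how long before T1 it is taken.

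**The concern.** The primary outcome is the only outcome scale without a T1 value. Its one scheduled pre-randomisation score is the score that admitted the participant, so it is cut off at 4. If change over time is measured from that score, two things follow.

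First, participants selected for a high score will on average score lower next time, whatever they receive. Each arm's fall from screening will then look like improvement that is partly an artefact of selection.

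Second, a group-by-time contrast that treats the screening score as an outcome row subtracts the whole of it. A model that conditions on the score subtracts only the part that predicts follow-up. The second is normally at least as precise, and the difference is largest when the correlation is low. That matters because the stated sample size has little power to spare.

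**Working it through.** **1. Reference power from the plan's own figures.** Sample size gives "Based on the average effect size of 0.27 for short term befriending outcome studies", "recruiting 172 participants per study arm (total of 344 participants) would achieve 80% power, with a statistical significance of 0.05", and "allowing for a higher than usual dropout rate of 20" per cent. Allocation is 1:1 ("randomised permuted block design with block size of two"). Sidedness is not stated.

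- Two-sided n per arm = 2 × (1.960 + 0.842)² / 0.27² = 215.3, or 216 with the usual small-sample allowance. Dividing by 0.8 gives 270, so 172 is not reproduced.
- Completers at 172 per arm: 172 × 0.8 = 137.6.
- Power at 137.6 per arm, ignoring baseline: Φ(0.27 × √(137.6/2) − 1.960) = Φ(2.240 − 1.960) = 61%.

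An unstated baseline adjustment with correlation 0.60 would come close: 215.3 × (1 − 0.60²) = 137.8, rounded up to 138, and 138/0.8 = 172.5, or 173. The article does not say that this was done. The sample size is a separate matter; here it only sets the reference.

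**2. Without a cut.** Let r be the correlation between the pre-randomisation and T3 scores, with equal variances. Relative to T3 alone, the variance is 2(1 − r) for change and 1 − r² for baseline adjustment. The ratio is 2/(1 + r): 1.54 at r = 0.3 and 1.11 at r = 0.8.

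**3. With entry at 4 or more.** The article gives no mean, SD or correlation, so all three are assumed. Scores are simulated as normal, rounded and clipped to 0–15, with mean 5 and SD 3.3 before the cut. Those with a first score of 4 or more are kept. The effect is held at 0.27 SD of the T3 score in those kept. Power comes from a two-sided two-sample test at 137.6 per arm, with effect 0.27/√(variance factor).

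| r before the cut | Variance factor, change | Variance factor, adjusted | Power, change | Power, adjusted |
|---|---|---|---|---|
| 0.4 | 1.12 | 0.92 | 56% | 64% |
| 0.5 | 1.02 | 0.87 | 60% | 67% |
| 0.6 | 0.89 | 0.79 | 66% | 71% |
| 0.7 | 0.76 | 0.69 | 73% | 76% |
| 0.8 | 0.58 | 0.55 | 83% | 85% |

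Example at r = 0.6. Change: 0.27/√0.89 = 0.286, and Φ(0.286 × 8.295 − 1.960) = Φ(0.41) = 66%. Adjusted: 0.27/√0.79 = 0.304, and Φ(0.304 × 8.295 − 1.960) = Φ(0.56) = 71%. Here 8.295 is √(137.6/2).

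The gain from adjustment runs from about 8 points at r = 0.4 to 2 at r = 0.8. At an assumed mean of 7 it reaches about 11 points at r = 0.4 (55% against 66%). At r of 0.5 or below, change from screening does no better than the 61% from ignoring baseline.

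**4. Fall without any treatment effect, same simulation.** At r = 0.6/0.7/0.8 the mean falls 0.70/0.53/0.37 points with mean 5, and 0.35/0.26/0.18 with mean 7. The same fall is expected in both arms.

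**5. The planned type of model.** Small simulations of a negative binomial GEE with exchangeable correlation used 138 per arm, SD 3 and 120 runs per setting. The group-by-time estimate had 0.97 to 1.17 times the variance of the baseline-adjusted one. Power was 67% against 70%, 83% against 85%, and 95% against 96% at r = 0.4, 0.6 and 0.8. A further run with the score cut at 4 gave variance ratios of about 1.13, 1.00 and 0.96. With 120 runs, a ratio of two independent variance estimates has a relative standard error of about √(4/120) = 0.18. It is smaller here because both models were fitted to the same data, but ratios this close to 1 are not clearly different from it. With no treatment effect, both models gave mean estimates near zero.

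**The case against.** The strongest reply is that the article does not say what the concern needs it to say. It adjusts for study covariates that it does not list, and the screening GDS-15 could be among them. A negative binomial model takes non-negative counts, so raw change scores cannot be its outcome; change over time is a passing description. A covariate list is the kind of detail that a condensed article leaves to an analysis plan. All of this stands. A reader might infer that the plan analyses change scores and refuses to adjust for baseline, and the text does not support that.

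A reader might also infer that selection on the outcome scale biases the trial's result. It does not: both arms pass the same cut before randomisation, and the aim is a comparison with usual care. Nor does the trial lack a baseline, since a score taken before randomisation is a valid one.

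It is also fair that the sentence before Table 1 may only be naming the columns (the Lubben scale is unticked at T2 under the same sentence), and that the larger power differences come from a Gaussian comparison at T3, which is not the planned model.

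What remains is that the table and text disagree about the primary outcome, that the baseline used in the analysis section is not defined, and that the one role given to baseline depression is not adjustment.

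**Conclusion.** The point holds as a low-cost improvement, not as a flaw that threatens validity. Table 1 schedules no T1 GDS-15, against its introductory sentence and against the mention of baseline depression in Data analysis. The natural reading makes the truncated screening score the first row of the outcome, though the article does not rule out adjustment.

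Within-arm falls should not be read as treatment benefit. The possible loss of precision is about 2 to 8 power points in a Gaussian T3 comparison (mean 5, correlation 0.8 down to 0.4) and up to about 11 at mean 7. In a negative binomial GEE it is small to nil unless the correlation is low. These figures rest on assumed means, SDs and correlations, none of which the article gives. Conditioning on the screening score does about as well or better across the range and protects against the low-correlation case.

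**What to change.** 1. State that the screening GDS-15 is the baseline for the primary outcome and when it is taken relative to T1 and randomisation. Correct Table 1, its introductory sentence and the Study design text to match.
2. Specify that the primary model uses T2 and T3 as outcome rows with the pre-randomisation GDS-15 as a covariate. An equivalent choice is to keep all three rows and constrain the arms' baseline means to be equal. Name the adjusted T3 difference as the treatment effect.
3. Report falls within each arm as descriptive only, with a note that entry required a score of 4 or more.

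This is wording only: it needs no new data and no extra recruitment, and should be fixed before anyone sees outcomes by arm. Repeating the GDS-15 at T1 for remaining participants is optional. It could add precision, but the gain depends on an unstated interval between screening and T1, and it would give an ongoing trial two definitions of baseline.

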#### Data storage

All hard copy data are stored in a coded (re-identifiable) form in a locked filing cabinet at the National Ageing Research Institute. All electronic data are coded (re-identifiable) and stored on a password-protected server at the National Ageing Research Institute. Trial data are only accessible by the research team, and the National Ageing Research Institute Research Governance Officer if necessary.

